### Data Collection and Statistical Analyses

Data will be collected at baseline, directly post surgery, after 2 months, and every 6 months after the operation until 2 years after skeletal maturity (see Table 1).

To describe the included patient group, patient characteristics such as age at surgery, sex, height, weight, medical and surgical history, blood loss during surgery, operative time, length of hospitalization, upper and lower level of fixation, short- and long-term complications (surgical site infections, neurological complications, implant failure, proximal junctional kyphosis, etc), and when applicable, secondary surgery (including the time between the first and second surgery) will be extracted from the patient's medical record. The data will be summarized in tables listing the mean, SD, median, minimum, maximum, and number of subjects for continuous data or in tables listing the quantities and percentages for categorical data, where appropriate.

For the primary goal, to analyze the efficacy of OWSER, the correction of the scoliotic curve will be measured by comparing the preoperative and postoperative Cobb angle with the Cobb angle 2 years after maturity. Radiological parameters will be measured by an orthopedic resident, trained to measure all radiological parameters. Measurements will be randomly verified by a senior experienced spine surgeon. Measured radiological parameters include the main Cobb angle (measured as defined by Cobb [21]), compensatory Cobb angle, correction after surgery, sagittal balance (thoracic kyphosis, lumbar lordosis, and proximal and distal junctional angle), pelvic parameters (pelvic obliquity, sacral slope, pelvic incidence, and pelvic tilt), Risser sign, and vertebral rotation based on full spine standing posterior-anterior and lateral radiographs. Differences between the Cobb angles and growth will be analyzed using repeated ANOVA measures. To correct for possible confounders, a mixed-model regression analysis will be performed including age at surgery, Risser sign, weight, and sex.

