### Sample Size

To perform a sample size analysis, we compared our study to the study conducted by Miladi et al [23]. The sample size calculation is based on an ANOVA analysis and calculated using the statistical program G*Power (Heinrich-Heine-Universität Düsseldorf) [24,25].

Miladi et al [23] reported the results from the precursor of our OWSER system from the higher thoracic spine to the pelvis in 100 patients with NMS. The mean Cobb angle improved from 89° (range, 25°-149°) to 35° (range, 6°-53°) 3 years after surgery [23]. No SDs were reported. In light of this study, we expect a Cobb angle of 35° at maturity. To use these numbers for the sample size calculation, we assumed a normal distribution of the data; as such, the SDs of the preoperative Cobb angle were 31 and 11.75 for the postoperative Cobb angle [26]. We assumed a correlation of 0.5 and an effect size of 0.4 based on the correction described by Miladi et al [23]. The sample size calculation indicated that 12 patients ought to be included to examine the significant difference between the preoperative Cobb angle and the Cobb angle at the latest follow-up (power: 80%, significance level: 0.05).

Additionally, 20% more patients were included to account for a possible loss of subjects in the follow-up. In conclusion, the highest sample size indicated was 12; therefore, the minimal sample size needed for this study to address the primary goal is 14 patients. After the inclusion is completed, a post hoc power analysis will be performed to conclude if a significant number of patients is included in the study.

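### The planned post hoc power analysis cannot show whether enough patients were enrolled; the confidence interval for the Cobb change can

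*Protocol article*

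**What the plan says.** The Sample Size section sets out an a priori calculation. "The sample size calculation is based on an ANOVA analysis and calculated using the statistical program G*Power", with "power: 80%, significance level: 0.05". The inputs are a correlation of 0.5 and an effect size of 0.4. The result is 12 patients, raised by 20% to 14, and 14 is described as a minimum. No maximum is given.

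The section then closes with the sentence at issue: after inclusion is completed, "a post hoc power analysis will be performed to conclude if a significant number of patients is included in the study". It does not name the effect size, SD or correlation to be used, the level of power that would count as enough, or what follows if the answer is no.

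Under Data Collection and Statistical Analyses, the primary goal is addressed by "comparing the preoperative and postoperative Cobb angle with the Cobb angle 2 years after maturity". The Results section hopes to close inclusion at the beginning of 2025 and expects first results at the beginning of 2024.

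**The concern.** The sentence gives a calculation made after enrolment the job of deciding whether the study was large enough. If the calculation uses the observed effect, it carries no information beyond the p value. A non-significant result will then always look under-sized, and a clearly significant one will always look adequately sized. If it uses the planned effect, it repeats what the design already fixed. Either way the report would contain a statement about sample adequacy that the method cannot support, in a single-arm study of 14 patients where the honest question is how precisely the Cobb change has been estimated.

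Two gaps add to this. If the calculation is run as soon as inclusion closes, recently enrolled patients will not yet have the outcome at 2 years after maturity. And with a minimum N, no maximum and no stated consequence, nothing says how an unfavourable answer would be handled.

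**Working it through.** **Inputs.** From Sample Size: effect size 0.4 (read as Cohen's f), correlation 0.5, alpha 0.05, N = 12 and 14, SDs 31 and 11.75. From the primary comparison: three time points (before surgery, after surgery, 2 years after maturity). Assumptions: three repeated measures with sphericity; a two-sided paired t test to illustrate observed power.

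**1. Reproducing the plan's figure.** Repeated-measures ANOVA, within factor: λ = f²·N·m/(1−ρ), df1 = m−1, df2 = (N−1)(m−1).
- N = 12, m = 3: λ = 0.16 × 12 × 3 / 0.5 = 11.52, df 2 and 22, power 0.816. N = 11 gives 0.773. So 12 is the smallest N that reaches 80%, which matches the plan.
- With m = 2, power at 12 is 0.714 and 15 patients are needed, so three time points is the reading that fits.
- Allowance: 12 × 1.2 = 14.4, stated as 14.

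**2. Power from the planned effect.** The same formula with m = 3 gives 0.816 at N = 12 and 0.882 at N = 14. Both follow from N alone and are available before the first patient is enrolled.

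**3. Power from the observed effect.** Set the noncentrality equal to the observed t and compute the probability of exceeding the critical t (2.201 at 11 df; 2.160 at 13 df).

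| p value | n = 12 | n = 14 |
|---|---|---|
| .01 | 0.807 | 0.795 |
| .05 | 0.519 | 0.516 |
| .20 | 0.238 | 0.240 |

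For a given n, each p value maps to one power. A result has to reach about p = .01 before observed power reaches 80%. An F test behaves in the same way, because the observed F fixes both the p value and the observed effect size.

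**4. How often observed power misjudges a correctly sized study.** At n = 12, true power of 80% needs a noncentrality of 3.078 (standardised change 3.078/√12 = 0.889). Observed power falls below 0.80 when |t| < 3.078. With that noncentrality, the probability is 0.474, about 47%. In simulation the 5th to 95th percentiles of observed power were about 0.25 to 0.999.

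**5. If more patients were added and the test repeated (hypothetical; not in the document).** Under no true change, testing at .05, adding patients if not significant, and retesting at .05 gives a type I error of about 7.8% for 12 then 18. For 14 then 21, separate simulation runs gave 7.7% to 7.9%.

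**6. Precision, which is what the question is really about.** Half-width of the 95% CI = t(0.975, n−1)/√n, in units of the SD of change:
- n = 14: 2.160/3.742 = 0.58
- n = 12: 2.201/3.464 = 0.64
- n = 11 (14 × 0.8 = 11.2): 2.228/3.317 = 0.67

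In degrees, the plan's own SDs and correlation give an SD of change of √(31² + 11.75² − 2 × 0.5 × 31 × 11.75) = 27.1°. The half-widths are then about 15.7°, 17.2° and 18.2°. These SDs are derived from the ranges in a neuromuscular series, so the values in degrees are illustrative for this population.

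**The case against.** **The inputs are not stated.** The analysis might combine the planned change with the observed SD and correlation. That would not be a function of the p value, and it would check planning inputs that the section admits are derived from ranges because no SDs were reported. This stands as a possible reading, and the full protocol may specify it. But it is a check of planning assumptions. It is served directly by reporting observed against assumed values, and the confidence interval already carries the resulting precision.

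**A reader might infer that the trial plans to extend enrolment.** The document does not support that. The analysis comes after inclusion is completed, and no section describes added patients, a retest or sample size re-estimation. A minimum without a maximum leaves the possibility open but is not a rule to extend. The sizes 18 and 21 are assumed for illustration.

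**The type I error figure has limited practical weight.** It assumes no true change. The plan's own figures ("The mean Cobb angle improved from 89° (range, 25°-149°) to 35° (range, 6°-53°) 3 years after surgery", with the SDs and correlation above) imply a standardised change of 54/27.1 = 1.99 and paired-t power above 0.999 at n = 12. If those figures carried over to this population, a non-significant result would be unlikely. This stands, and is a reason not to lead with that figure.

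**A reader might also infer that the calculation must rest on early postoperative correction.** The text gives an earliest point, not a date, and the calculation could accompany the final analysis. The missing primary outcome is a problem only if it is run when inclusion closes.

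**The sentence alters no estimate or test.** True; the primary analysis stands without it. It does alter what the report will claim about its own size.

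**Conclusion.** The concern holds in a limited form. The plan commits to a post hoc power analysis for a purpose it cannot serve under either main reading. Observed-effect power restates the p value (0.52 at p = .05 with n = 12) and would label a study with true 80% power too small about 47% of the time. Planned-effect power (0.82 at 12, 0.88 at 14) is known in advance.

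These figures rest on a paired t illustration and on three time points in the planning model. The rise in type I error to about 8% is conditional on an extension that the document does not plan. The problem of missing primary outcomes is conditional on the calculation being run as soon as inclusion closes. The point affects how the result will be interpreted, not the validity of the primary test, and should be corrected before the results are reported.

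**What to change.** Delete the post hoc power sentence and replace it with wording along these lines: *Precision will be judged from the 95% confidence interval of the mean change in main Cobb angle from before surgery to 2 years after maturity, read in degrees. The expected half-width is 0.58 SD of the change with 14 evaluable patients, 0.64 with 12 and 0.67 with 11. Enrolment will not be extended on the basis of observed results.*

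It would help to say what half-width in degrees the team regards as adequate, since the interval alone does not define that. If the planning SD and correlation are to be checked, report them as observed against assumed, without computing power from the observed effect.

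The cost is an edit to the text. An analysis is removed, and no patient, visit or measurement changes.

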## Results

Patient inclusion started on November 17, 2021, and we hope to finalize patient inclusion by the beginning of 2025. The first results will be expected by the beginning of 2024. On October 14, 2023, a total of 5 patients have undergone surgical correction with the proposed surgical technique. We aim to publish the 2-year results of these patients in May 2024.

## Discussion

### Principal Findings

Currently, all patients with AIS and diagnosed with curves exceeding 40° to 45° are recommended surgical correction followed by PSF to fix the patients’ spine for the rest of their lives [2,3]. In this study protocol, we describe a protocol to investigate the safety and efficacy of a minimally invasive posterior bipolar nonfusion OWSER for the surgical treatment of patients diagnosed with AIS.

The concept of PSnF for scoliosis surgery is not new. For patients diagnosed with EOS and NMS, multiple successful PSnF options are available and are currently regarded as the standard surgical treatment [16]. However, to the best of our knowledge, this concept has not been used in patients diagnosed with AIS.

The aim of this prospective study is to determine the efficiency and safety of the implant by analyzing radiological parameters (primarily Cobb angle), patient satisfaction scores, and complication rates. The expected primary benefit of this surgical technique is an efficient surgical correction of the Cobb angle without PSF. Because of the minimally invasive character of the surgical procedure, the spinal structures of the apex of the curvature between the thoracic and lumbar anchor points are not altered. Although some cases of auto-fusion have been described when using minimally invasive surgery [14], to the best of our knowledge, no complete full spinal fusion will occur. This might only allow the removal of the nonfusion OWSER at the end of spinal growth in patients in which the curve remains stable for a longer period of time and remains under 30° [27]. In addition, the system allows for a natural correction of the spinal deformity while the correct balance and alignment of the spine are maintained. Because of its self-expanding function, the system allows the patient to follow its final natural growth while functioning as an “internal brace.” Finally, due to the minimally invasive nature of the surgical procedure, the overall surgical time and general anesthesia time will be reduced, and the scar length can be limited to two scars that are 5-10 cm in length at the thoracic and lumbar fixation level.

For patients diagnosed with NMS, the positive long-term results of a nonfusion OWSER were described by Gaume et al [20] in 2021. The original nonfusion OWSER provides instrumentation for NMS from T1 to the sacrum. In patients with AIS, however, instrumentation is only needed for the length of the structural curve. Therefore, we suggest inserting the notched rod at the end of the caudal part of the construct. Hereby, the thoracolumbar approach is performed using a smaller incision. The OWSER instrumentation elongates and corrects the deformity spontaneously alongside the natural growth of the patient, allowing spinal balance correction; it does not touch the apex vertebrae of the spinal curvature and prevents complete PSF. The OWSER instrumentation can be considered an “internal brace.”

Although positive long-term results have been published following PSnF surgery in patients with NMS, complications have been recognized. Gaume et al presented their preliminary results of the use of a minimal invasive OWSER for the treatment of patients with NMS. They found an overall complication rate of 38% (n=8), consisting of 14% (n=3) mechanical complications and 24% (n=5) infectious complications [20]. Although these complication rates seem high, compared to the traditional growing techniques, there is an important decrease in complication rates [28].

All of the included patients were fixed from the high thoracic level up to the pelvis. Our patient population will arguably be fixed over a shorter number of vertebrae, lowering the amount of force distributed over the system. In addition, Gaume et al [20] found a postoperative infection rate of 24% (n=5) directly post surgery. In postoperative patients diagnosed with AIS, this would be unacceptable. However, these results cannot be directly translated to our patient population, as it is known that patients with NMS have poor general status [29]. This makes them more prone to infectious complications as compared to the healthy patients with AIS who will be included in this study.

Other possible complications are an inherent part of spinal surgery, such as intraoperative cardiologic complications and neurological complications. The risk of neurological complications will be minimized using intraoperative neuromonitoring via both MEP and SSEP during the surgical procedure. All AE and SAE are monitored based on the guidelines of the Dutch Ethics Committee, and will help determine the safety of the proposed surgical technique.

The absence of a control group could be seen as a potential limitation. In this study, we do not have a control group as we focus on the efficiency and safety of the surgical device. If the device is proven to be efficient and safe, a follow-up will be proposed to compare the postoperative results between the nonfusion OWSER system and the traditional PSF. In addition, this would allow us to discuss the cost-effectiveness of the PSnF surgery compared to the traditional PSF surgery.

### Conclusions

In conclusion, this study is designed to evaluate the efficiency and safety of the surgical treatment with a bilateral bipolar OWSER implant in patients with progressive AIS. We hypothesize that the system is safe and efficient in the surgical treatment of AIS, while it serves as an “internal brace,” allowing the patients to follow their natural growth and individual balance. To the best of our knowledge, this is the first study to investigate the potential efficacy and benefits of the use of the nonfusion OWSER in patients diagnosed with AIS who failed conservative treatment.

## Abbreviations

AE: adverse event
AIS: adolescent idiopathic scoliosis
EOS: early-onset scoliosis
GDPR: General Data Protection Regulation
MEP: motor-evoked potential
NMS: neuromuscular scoliosis
nonfusion OWSER: nonfusion one-way self-expanding rod system
OWSER: one-way self-expanding rods
PSF: posterior spinal fusion
PSnF: posterior spinal nonfusion
SAE: serious adverse event
SRS-22r: Scoliosis Research Society's-22r
SSEP: somatosensory-evoked potential
UMC: University Medical Center
